# Study protocol: pragmatic randomized control trial of my tools 4 care- in care (MT4C-in care) a web-based tool for family Carers of persons with dementia residing in long term care

**DOI:** 10.1186/s12877-020-01690-w

**Published:** 2020-08-10

**Keywords:** Carers, Dementia, Pragmatic trial, Online intervention, Long term care

## Abstract

**Background:**

When a family member resides in long term care facility (LTC), family carers continue caregiving and have been found to have decreases in mental health. The aim of My Tools 4 Care – In Care (an online intervention) is to support carers of persons living with dementia residing in LTC through transitions and increase their self-efficacy, hope, social support and mental health. This article comprises the protocol for a study to evaluate My Tools 4 Care-In Care (MT4C-In Care) by asking the following research questions:
Is there a 2 month (immediately post-intervention) and 4 month (2 months post-intervention) increase in mental health, general self-efficacy, social support and hope, and decrease in grief and loneliness, in carers of a person living with dementia residing in LTC using MT4C-In CARE compared to an educational control group?Do carers of persons living with dementia residing in LTC perceive My Tools 4 Care- In Care helps them with the transitions they experience?

**Methods:**

This study is a single blinded pragmatic mixed methods randomized controlled trial. Approximately 280 family carers of older persons (65 years of age and older) with dementia residing in LTC will be recruited for this study. Data will be collected at three time points: baseline, 2 month, and 4 months. Based on the feasibility study, *we hypothesize that participants using MT4C-In Care will report significant increases in hope, general self-efficacy, social support and mental health quality of life, and significant decreases in grief and loneliness from baseline, as compared to an educational control group*. To determine differences between groups and over time, generalized estimating equations analysis will be used. Qualitative descriptive analysis will be used to further evaluate MT4C-In Care and if it supports carers through transitions.

**Discussion:**

Data collection will begin in four Canadian provinces (Alberta, Manitoba, Ontario and Saskatchewan) in February 2020 and is expected to be completed in June 2021. The results will inform policy and practice as MT4C-In Care can be revised for local contexts and posted on websites such as those hosted by the Alzheimer Society of Canada.

**Trial registration:**

NCT04226872 ClinicalTrials.gov Registered 09 January 2020

Protocol Version #2 Feb 19, 2020.

## Background

In 2018 in Canada, 564,000 people were living with dementia, and this number is expected to almost double by 2031 [1]. Dementia affects not only the person living with the disease, but their families, friends, and communities. In particular, family and friend carers (hereafter referred to as ‘carers’) are challenged to cope with the many transitions that occur across all stages of dementia. For these carers, transitions involve learning new tasks, making significant adaptations to the physical and/or social environment, and changing their roles and relationships [2]. Although carers have positive experiences as a result of these significant changes, many carers experience significant physical and mental health challenges, including distress and burnout [3].

Little is known about the transition experience, support needs, and effective interventions for carers after their family member with dementia moves to a 24-h long-term care (LTC) community [4, 5]. Caregiving continues when family members of persons living with dementia reside in LTC; in fact, this time period is often characterised by continued involvement, during which carers must learn multiple new roles and make significant and often stressful adjustments [4–6]. Carers of a family member living with dementia in a LTC community are an at-risk group**,** and evidence suggests that carers’ mental health may actually worsen after their relative with dementia moves to LTC [7]. Carers may report feelings of blame, self-doubt, loneliness, isolation, and powerlessness [4, 7] which negatively affect their mental health [8]. In contrast, hope, confidence in the ability to deal with difficult situations or self-efficacy, and social support can improve their mental health.

Transitions are significant changes experienced by an individual that are incorporated into their lives [9]. Carers of older persons living with dementia residing in LTC experience multiple complex transitions, such as changes in roles and relationships, physical and mental health, and hope [2]. Social support influences feelings of loneliness and mental health [10], and may improve one’s ability to cope with stress during times of transition [11]. Social support is a function of a person’s social network, and may be instrumental (e.g., tangible services), emotional (e.g., expressions of empathy), informational (e.g., advice) or appraisal support (e.g., information useful for self-evaluation) [12]. Interventions that support carers in dealing with transitions are essential for their quality of life.

Due to the costs, and sometimes limited accessibility associated with face-to-face interventions, there is a shift towards technology-driven interventions to support carers [13–15]. Three reviews have been published on web-based interventions for carers of persons living with dementia [13–15]. Boots et al. [14] in their review of 12 studies concluded that multi-component online interventions that were flexible and tailored to the individual resulted in increased carer well-being. These conclusions are similar to those of reviews of online interventions for carers of people living with a variety of diagnoses, including dementia [16–18]. The reviewed studies suggest that web-based interventions show promise in increasing the mental health of carers. However, none of the reviewed interventions were specifically tailored for carers of persons living with dementia in the context of LTC.

Two multi-component web-based interventions to support carers of persons living with dementia have been developed by our research team. They are based on Meleis’ transition theory [19] and combine information and interactive activities tailored to carers of persons living with dementia. The first intervention (My Tools 4 Care; https://www.mytools4care.ca) was developed for carers of persons living with dementia in the community [14]. My Tools 4 Care was recently evaluated using a pragmatic randomized control trial [20] and had a significant positive impact on participants’ hope, as compared to an educational control group. Hope has also been found to have a significant positive relationship with mental health in this population [2].

Carers of older persons living with dementia residing in LTC approached us to adapt My Tools 4 Care for their use. The experiences of carers of persons living with dementia in the community and those in LTC appear to share some similarities. For example, carers of persons living with dementia residing in LTC continue to experience loss [21] and significant changes in hope [22]. However, many differences are also apparent. For example, negative interactions between carers and LTC staff and poor perceptions of care have a negative impact on carers [7, 23], potentially resulting in an increased need for healthcare services. Moreover, carers in LTC are concerned about end-of-life decision-making [16].

Working with carers, the research team developed My Tools 4 Care-In Care (MT4C-In Care; https://www.mytools4careincare.ca) for use with carers of a person with dementia residing in LTC. MT4C-In Care is a self-administered, multicomponent, flexible, and interactive website. MT4C-In Care aims to support carers of persons living with dementia to adapt to the significant transitions they face after their relative has moved to a LTC setting by increasing hope, self-efficacy, and social support, and decreasing grief and loneliness. Throughout the website, the user is prompted to mobilize their existing support networks to obtain social support (e.g., identifying people who give one strength or discussing carer goals with facility staff). As a resource provided by the carer’s social network (e.g., the local Alzheimer Societies), MT4C-In Care also delivers support directly. For example, MT4C-In Care offers emotional support (e.g., statements aimed to validate feelings of guilt), information support (e.g., fact sheet on ways to address loneliness), and appraisal support (e.g., prompts to reflect on experiences as a carer).

A feasibility study of MT4C-In Care with 37 participants demonstrated an increase in hope (*p* = 0.006) and decrease in grief (*p* = 0.005) from baseline to a time point 2 months later [24]. Although statistically significant differences in mental health were not detected, hope (r = 0.43, *p* = 0.027) and grief (r = − 0.66, *p* = 0.00) were significantly related to mental health. Whether social support and loneliness mediate the effects of MT4C-In Care upon mental health has not been evaluated to date. Prior to this pragmatic trial, we conducted focus groups with carers in four Canadian provinces to optimize the tool’s ability to improve carers’ perceptions of social support. Based on the feasibility study and focus groups, below is a diagram of the MT4C-In Care framework (Fig. 1) in which we hypothesize that MT4C-In Care increases hope, general self-efficacy and social support, and decreases grief and loneliness. Through these mechanisms, the tool increases mental health of carers of older persons living with dementia residing in LTC.

**Fig. 1 Fig1:**
[figure not shown]
Conceptual Framework for MT4C-In Care. Conceptual framework of the proposed mediators (proximal outcomes) and primary (distal) outcome of MT4C-In Care

### Purpose

The purpose of this study is to evaluate whether use of MT4C-In Care over 2 months is effective to decrease loneliness and grief, and increase hope, general self-efficacy, social support and mental health as compared to an educational control group. It will address the following research questions:
Is there a 2 month (immediately post-intervention) and 4 month (2 months post-intervention) increase in mental health, general self-efficacy, social support and hope, and decrease in grief and loneliness, in carers of a person living with dementia residing in LTC using MT4C-In CARE compared to an educational control group?Do carers of persons living with dementia residing in LTC perceive My Tools 4 Care- In Care helps them with the transitions they experience?

## Methods/design

### Study design

This pragmatic mixed methods randomized controlled trial is longitudinal, multi-site, and involves repeated measures. Participants are randomly assigned to an intervention or control group using REDCap, a secure, password-protected web application housed by the University of Alberta. The intervention group receives an educational resource and access to MT4C-In Care over a two-month period. The educational control group also receives the educational resource but will not be granted access to MT4C-In Care until the study period is over. Recruitment and data collection are planned between February 2020 and June 2021 in four provinces (Alberta, Saskatchewan, Manitoba and Ontario). Outcome data collection will occur at baseline, and 2 and 4 months from the start of the intervention. Process data collected at 2 and 4 months include qualitative data related to participant perceptions of MT4C-In Care and quantitative data related to frequency of use. Quantitative and qualitative data related to study processes (e.g., frequency and reasons for missing data) will be collected concurrently throughout the study. The qualitative data will help to explain the quantitative findings.

Reporting of this protocol followed the SPIRIT (Standard protocol items: recommendations for interventional trials) [25] guidelines for reporting protocols (SPIRIT checklist in supplementary files). This study received ethical approval from the University of Alberta Health Research Ethics Board (#Pro00090771), University of Saskatchewan Research Ethics Board (#1385), Education/Nursing Research Ethics Board at the University of Manitoba (E2019:127), and the Hamilton Integrated Research Ethics Board (#7659). If there are any changes in the protocol an amendment will be sent to the respective ethics boards for approval.

### Participants/settings

Carer is defined broadly as unpaid family or friends who provide any form of care to someone living with dementia. This care can include, but is not limited to, assisting with personal care, taking food, arranging appointments, and advocating for their relative. Carers will meet the following inclusion criteria: 1) English-speaking; 2) ≥ 18 years of age; 3) provides physical, emotional, or financial care to persons living with dementia who is ≥65 years of age and lives in a LTC home; and 4) has an email address and access to a computer with internet. Exclusion criteria are: 1) care partner is no longer living; 2) care partner resides in the community; and 3) care partner is currently hospitalized or in an assisted living facility.

Participants in four provinces in Canada (Alberta, Saskatchewan, Manitoba and Ontario) will be asked to participate in the study via telephone. The setting will be of their choosing, so that they can participate from their homes, or wherever they feel most comfortable.

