### Recruitment and randomization

Advertisements in local community newspapers which direct potential participants to contact the research coordinators (one in each province) via email or a toll-free number will be used to recruit participants. As well, LTC facilities and the Alzheimer Societies of Brant, Haldimand Norfolk, Hamilton Halton, Manitoba, Saskatchewan, Alberta/North West Territories, and Calgary, will assist with recruiting potential participants.

Research assistants will contact potential participants in each province via telephone to explain the study, answer any questions, and obtain informed verbal consent to participate. A tracking sheet of the numbers of potential participants who are approached to participate in the study, as well as the number of eligible consenters and non-consenters will be kept in a secure shared drive separate from the data. Reasons for non-consent will be documented.

A unique study identifier will be assigned to each participant to maintain confidentiality. REDCap will be used to randomly assign (1:1 ratio) participants to either the intervention or control group. Participants will be blinded to assignment status, and will be told that they will be offered one of two ways of providing support. In order for blinding to occur, the control group will be an educational control group receiving educational information. Two versions of the consent forms will be used one for the intervention and another for the control group (both versions of the consent forms are in the supplementary file). The RAs will read to the participants the version of the informed consent that will describe the study and group allocation procedures specific to their assigned group. Following the first interview, the informed consent will be emailed to participants. Data collection will then proceed with gathering demographic data and the baseline survey measures. Immediately following the baseline interview, all participants will be sent a copy of the appropriate consent form by email. Un-blinding will occur upon the request of the participant.

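### Eligibility sets no limit of one carer per resident and carers are randomised individually, so co-carers of one resident could be placed in opposite arms

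*Protocol article*

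**What the plan says.** The Participants/settings section opens with a wide definition: "Carer is defined broadly as unpaid family or friends who provide any form of care to someone living with dementia". It then numbers four inclusion and three exclusion criteria. The inclusion criterion that ties a carer to a resident reads "provides physical, emotional, or financial care to persons living with dementia who is ≥65 years of age and lives in a LTC home". It asks for some care, not for being the main carer. The exclusion list begins "Exclusion criteria are: 1) care partner is no longer living; 2) care partner resides in the community", and its third item is also about where the person with dementia is. No criterion deals with a second carer of the same resident.

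The Recruitment and randomization section makes the individual the unit of allocation: "REDCap will be used to randomly assign (1:1 ratio) participants to either the intervention or control group". The study identifier is assigned per participant, and no linking or joint allocation of carers of one resident is mentioned. On blinding, it says "Participants will be blinded to assignment status, and will be told that they will be offered one of two ways of providing support". It also says "Two versions of the consent forms will be used one for the intervention and another for the control group", and each participant is read and emailed the form for the assigned arm.

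Under Study design, controls are kept off the website until the study period ends. Under the intervention heading, each user gets individual login details valid for two months.

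**The concern.** Two relatives of one resident can each satisfy every listed criterion, and independent allocation then separates some of them. This puts two things at stake.

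- **The control contrast.** A control whose relative has the website may see it or hear what it contains. Any benefit that the control takes from it moves the group difference in the MCS and in the secondary outcomes toward zero.
- **The blinding.** The abstract calls the trial single blinded. Research assistants read out the arm-specific consent text and research assistants also collect the outcome data, so participant blinding is the only blinding described. It works by not letting participants know what the other arm is offered. Two relatives in opposite arms hold different consent forms, and one of them holds a login, so comparing emails would show which arm each is in. The primary and secondary outcomes are all self-reported.

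**Working it through.** **1. Inputs from the Protocol article.** 280 carers, 140 per arm, 1:1 allocation of individuals; 89% power; alpha 5%; a 15% difference; 30% in group 2; three measurements; compound symmetry with within-subject correlation 0.50 (Power and sample size).

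**2. Inputs assumed.** The documents give neither of these, so ranges are used:
- f, the share of the 280 carers who enrol as one of a pair from the same resident: 5% to 20%.
- k, the share of the treatment effect that an exposed control receives: 0.5 or 1. The value 1 is an upper bound.

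**3. The plan's own figure.** Averaging three measurements under compound symmetry gives a variance factor of (1 + (3 − 1) × 0.5)/3 = 2/3, so the effective n per arm is 140/(2/3) = 210. A two-sided 5% comparison of proportions 0.45 and 0.30 with pooled variance gives

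z = (0.15 × √210 − 1.96 × √(2 × 0.375 × 0.625)) / √(0.45 × 0.55 + 0.30 × 0.70) = (2.174 − 1.342)/0.676 = 1.23,

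which is a power of 89.1%. The stated 89% is reproduced. This is a two-proportion model, whereas the Outcome analysis section treats the MCS as continuous, so the powers below are illustrative only.

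**4. Split pairs.** The number of pairs is 280f/2. Independent 1:1 allocation splits a pair with probability 0.5, giving 70f split pairs, each with one control. As a share of controls this is 70f/140 = f/2. The same share of the intervention arm has a relative in the control arm.

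**5. Dilution.** If a fraction f/2 of controls receives a share k of the effect, the observed difference is (1 − kf/2) times the true one. Power is recomputed with 0.15 × (1 − kf/2) above 0.30.

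| f (assumed) | Exposed controls | Share of 140 | Effect kept, k = 0.5 / 1 | Power, k = 0.5 / 1 |
|---|---|---|---|---|
| 5% | 3.5 | 2.5% | 0.9875 / 0.975 | 88.3% / 87.5% |
| 10% | 7 | 5% | 0.975 / 0.95 | 87.5% / 85.9% |
| 20% | 14 | 10% | 0.95 / 0.90 | 85.9% / 82.1% |

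**6. Standard errors.** Correlation between co-carers raises the variance of the group difference for pairs in the same arm and lowers it for split pairs. Under individual allocation the two kinds are expected in equal number, so they roughly offset. The issue is therefore dilution and unblinding, not the precision of the estimate.

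**The case against.** The strongest reply is that this is an argument from silence. The article condenses a full protocol (Trial registration cites version 2) that could hold a one-carer rule. That possibility stands. But eligibility appears here as numbered lists, it is not a matter that an article usually leaves to another document, and nothing in the text points to such a rule.

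Several stronger readings are tempting, and the documents do not support them.

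- A reader might infer that the website acts on a control relative directly, because "the user is prompted to mobilize their existing support networks to obtain social support". The Background does not say that this network is the co-carer. One of its two examples is talking with facility staff. The control group's educational document also prompts carers to seek support, so such prompting is not confined to the intervention arm.
- A reader might infer that recruitment brings in families together, since help comes from "LTC facilities and the Alzheimer Societies of Brant, Haldimand Norfolk" and other societies. The section says only that these bodies assist. The newspaper route asks individuals to make contact.
- A reader might take contamination as certain, or take the full carry-over figures as expected. Login details are individual, and even intervention participants may choose not to open the site. Full carry-over to every exposed control is a ceiling.
- A reader might suppose that blinding collapses for the whole trial. Participants already know what they themselves receive, and unblinding on request is allowed. What is masked is the other offer, and split pairs could reveal it to 2.5% to 10% of each arm on the assumed range, if they compare.

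**Conclusion.** The gap is real and modest. As written, the plan lets co-carers of one resident enrol and be split across arms, with no stated safeguard beyond individual logins. Harm arises only if such pairs enrol and then talk or share, and the documents give no frequency for either.

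With 5% to 20% of carers in pairs, the effect shrinks by at most 2.5% to 10%, and by about half that with half carry-over. In the illustrative model, power falls from 89.1% to between 88.3% and 85.9% at half carry-over, and to 82.1% in the worst case shown. At 10% or fewer in pairs the loss is at most about 3 points, so the threat to blinding may matter more than the power. The conclusion rests on the two assumed ranges and on the full protocol holding no one-carer rule. It is worth correcting because the correction is cheap.

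**What to change.** Add to the criteria in Participants/settings that only one carer per resident may be enrolled, namely the first who makes contact. At the screening call, the research assistant asks whether another carer of the same resident is already in the study. The cost is one question, one sentence, an ethics amendment (for which Study design already provides) and the loss of a few otherwise eligible second carers, a small narrowing for a pragmatic trial. If 280 are still recruited, the planned power does not change.

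For co-carers already randomised, record a resident identifier so that split pairs can be found. Keep them in the intention-to-treat analysis and add a sensitivity analysis that leaves out both members of each split pair. Clustering the GEE on resident deals only with correlation. It removes neither dilution nor unblinding and should not be offered as the remedy.
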